### Primary study outcome

*Maternal sensitivity* is the core experimental variable that COS-P aims to enhance. Sensitive responses, the ability to respond appropriately to the child’s attachment needs [67], has consistently been found to be the most reliable predictor of attachment security [64, 68, 69]. Maternal sensitivity is observed during 5 minutes mother-infant interaction (free play), and will be assessed during the home-visit at T0 and during the lab-visit at T1. The “Coding Interactive Behavior” (CIB) [70] will be used to code maternal sensitivity. The CIB is a global rating system for social interactions that includes 52 codes rated on a scale of 1 to 5 which are aggregated into several composites. The system has been validated in multiple longitudinal studies of normative and high-risk populations in infancy, preschool, and adolescence interacting with mother, and has shown adequate psychometric properties, including construct validity, test–retest reliability, and predictive validity [71–75]. All mother-infant interactions will be video recorded and coded by reliable coders blind to treatment allocation and with no clinical involvement in the study. Inter-coder agreement will be calculated on a randomly selected subset of 20% that will be coded by another reliable coder blind to treatment allocation.

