### Secondary study outcomes

*Infant*-*mother attachment quality* is the second core experimental variable in COS-P. Infant-mother attachment is generally thought to reflect how well toddlers are functioning in the relationship with their primary caregiver. Moreover, infant-mother attachment quality has been documented to play a crucial role in the child’s subsequent social and emotional development [6, 10, 11, 76]. Infant-mother attachment is observed at T1 in UCPH Babylab and assessed with The Strange Situation Procedure (SSP) [19, 20]. SSP is the most widely used and well-validated experimental paradigm for assessing the quality of the child’s attachment to a parent in infancy [10, 11, 76]. From the SSP, that is being video recorded, the child is observed in eight consecutive brief episodes that are designed to evoke mild stress to trigger the attachment behavior of the child. During the eight episodes (each of a maximum duration of 3 minutes) the mother and child are introduced to an unfamiliar room. Then a stranger enters the room and the child is separated two times from his/her mother as the mother leaves the room. The child’s attachment behavior is coded from the reunion episodes based on four interactive behavior scales: proximity-seeking, contact-maintaining, avoidance of the caregiver and resistance.

Continuous measures of attachment security and disorganization (in both infants and adults) have been suggested to be better suited than the categorical measures when subtle differences in attachment security and disorganization cannot be detected using the categorical approach [77–79]. Following IJzendoorn and Kroonenberg [80], we will therefore calculate a continuous attachment score from the four interactive scales used for the classification of the conventional attachment categories. Higher scores indicate more attachment security. This approach has been further validated in recently published studies [81, 82]. Continuous scores for disorganization will be derived directly from coding the conventional 9-point Disorganization scale [20] with higher scores indicating more disorganized behavior.

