*The Ages and Stages Questionnaires* –*Social*-*Emotional*, ASQ-SE [87] will be used to asses infant socio-emotional development at T1. Both mothers and fathers will be asked to fill in the questionnaire, and maternal and paternal report will be analyzed separately. Domains being assessed are Self-regulation, compliance, communication, adaptive functioning, autonomy, affects and interaction with people. The ASQ-SE is developed as a screening instrument, but is also used for monitoring progression. For the present study, the ASQ-Se has been translated with permission from the authors according to scientific standards, with two independent translations which were compiled, pilot tested in a sample of Danish parents, adjusted after interviewing these parents, back-translated by a native English speaker blind to the original version, and back-translation finally approved by Brooks Publishing.

*Bayley Scales of Infant and Toddler Development 3rd Edition* -*Screening Test*, *BSID III* (Pearson, 2008) will be used to assess infant cognitive development (T0 and T1) and infant language development (T1). The BSID is a standardized norm-based test widely used to assess general indices of infant mental development. The cognitive scale assesses memory and problem solving, exploration and manipulation, object relatedness, and sensorimotor development. The language scale is a composite of two subscales: an expressive scale (babbling, gesturing and utterances) and a receptive communication scale (verbal comprehension and vocabulary). Raw scores for each subscale are converted into scaled scores (range 1–19, *M* = 10, *SD* = 3), and a composite score (*M* = 100, *SD* = 15) can be derived from the scaled score for cognitive development, and the sum of the two language scaled scores. The test will be administered by trained psychologist who are routinely supervised based on video recordings of the tests. For inter-rater agreement, a randomly selected subset of 50% of the tests will be coded from video-recordings by a trained psychologist blind to group status and with no clinical involvement in the study.

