Secondary endpoints where a baseline value is available will be analyzed in the same way as the primary endpoint, see above. Binary outcomes will be analyzed by logistic regressions and continuous outcomes by linear regressions. For secondary endpoints where no baseline is available the analyses will only be adjusted for the family characteristics mentioned above. GEE techniques will be used throughout Significance will be assessed both using a 5% significance level and adjusted for multiple testing (6 tests planed) by the Holm–Bonferroni method. Findings significant even after correcting for multiple testing will be treated as truly significant findings while findings with *p*-values below 5%, but not significant after correcting for multiple testing will be described as potential significant findings.

The final secondary endpoint on heterogeneity of effects of COS-P across family types will be assessed by including an interaction term between group membership and family type (family types are: 1) Infant socially withdrawn; 2) Infant socially withdrawn AND maternal depression; and 3) Maternal depression only in the linear regression planned for the primary analysis.

For both logistic regressions and linear regressions model fit will be assessed by graphical procedures. In case of poor model fit additional sensitivity analyses and bootstrap procedures will be employed to establish if the findings of the study are sensitive to the lack of model fit. A detailed statistical analysis plan will be completed before half of the intended sample size has been recruited.

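### The covariate rule for outcomes without a baseline leaves T0 maternal sensitivity out of the attachment models and gives up some precision

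*Protocol article*

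**What the plan says.** Statistical methods sets two covariate rules for secondary endpoints. Where the endpoint has its own T0 value: "Secondary endpoints where a baseline value is available will be analyzed in the same way as the primary endpoint, see above". The primary model regresses the T1 value on treatment group and the T0 value. Where it does not: "For secondary endpoints where no baseline is available the analyses will only be adjusted for the family characteristics mentioned above".

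Table 1 shows three outcomes measured at follow-up only: SSP attachment, ASQ-SE and Bayley language. The second rule therefore governs these three.

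The article has no list titled family characteristics. The nearest match is Background information and control variables, which includes risk condition, infant age, depression status, parental attachment style and family functioning, among others. It does not include T0 CIB sensitivity. Statistical methods also names T0 sensitivity and the family characteristics as separate items, a) and b), when it describes adjustment of the primary effect size. T0 sensitivity is thus not one of the family characteristics.

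Under Primary study outcome, maternal sensitivity "will be assessed during the home-visit at T0 and during the lab-visit at T1", and the article says that it "has consistently been found to be the most reliable predictor of attachment security". Under Secondary study outcomes, attachment is ranked second among the core variables of the programme, and continuous security and disorganisation scores are planned.

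**The concern.** The plan accepts baseline adjustment for every secondary endpoint that has its own T0 value. Attachment loses it only because the same instrument was not used at T0, although the article names a strong baseline predictor and collects it. The word *only* is a stated restriction, so this is not a detail left open.

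At stake is the precision of the attachment comparison. The sample size was set for maternal sensitivity with an assumed baseline correlation of 0.5. Attachment has no comparable covariate, so it is tested with less information than the trial will hold.

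**Working it through.** **Inputs from the article:** 250 dyads in the final analysis; 2:1 allocation; two-sided 5% level; CIB SD 0.9; T0–T1 correlation 0.5 for CIB sensitivity; 200 dyads for 90% power at an effect of around 0.40 with clustering ignored.

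**Assumed:** the partial correlation ρ of T0 sensitivity with the T1 attachment score, given the family characteristics. The documents give no value. A range of 0.1 to 0.4 is used.

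**The plan's own figure first.** With baseline adjustment the residual SD is 0.9 × √(1 − 0.5²) = 0.779. For 200 dyads at 2:1, √(1/66.7 + 1/133.3) = 0.150. The effect detectable with 90% power is (1.960 + 1.282) × 0.779 × 0.150 = 0.379, which fits the stated figure of around 0.40. At exactly 0.40 raw points the power is 92.8%. The point below does not depend on this figure.

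**Gain from adding the covariate, 250 dyads, 2:1, clustering ignored.**

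- Standard error reduction: 1 − √(1 − ρ²).
- Equivalent extra dyads: 250 × [1/(1 − ρ²) − 1].
- Detectable effect at 90% power, in units of the residual SD before the covariate is added: (1.960 + 1.282) × √(1/83.3 + 1/166.7) × √(1 − ρ²) = 0.435 × √(1 − ρ²).
- Power is shown for 0.40 of those SD units. This value is chosen for illustration; the article sets no target effect for attachment.

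| ρ (assumed) | SE reduction | Extra dyads | Detectable effect | Power at 0.40 SD |
|---|---|---|---|---|
| 0 (current rule) | – | – | 0.435 | 84.6% |
| 0.1 | 0.5% | 2.5 | 0.433 | 85.0% |
| 0.2 | 2.0% | 10.4 | 0.426 | 86.1% |
| 0.3 | 4.6% | 24.7 | 0.415 | 87.8% |
| 0.4 | 8.3% | 47.6 | 0.399 | 90.2% |

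Power is at the unadjusted 5% level. It would be lower in every row under the Holm–Bonferroni correction planned for the secondary tests.

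**The case against.** The strongest reply is that nothing here is invalid. In a randomised comparison of continuous outcomes, leaving out a prognostic covariate neither biases the estimate nor inflates the type I error rate, and the confidence interval already allows for chance imbalance. That stands, and it limits the point to efficiency.

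The size is also uncertain. Calling sensitivity the most reliable predictor ranks it and gives no magnitude. T0 spans 2 to 12 months of age, and the family characteristics already include risk condition, depression status and parental attachment style, which may absorb part of the gain. This stands too, and it is why the range starts at 0.1, where the gain is negligible.

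It can also be said that a detailed analysis plan is still to come. That carries less weight: the article does not leave the covariates open, it states a restrictive rule that the later plan would have to change.

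A reader might infer more than the article supports:

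- **That it calls Bayley cognition predictive as well.** It does not. It says only: "The BSID is a standardized norm-based test widely used to assess general indices of infant mental development". Nor does it call T0 sensitivity a predictor of Bayley language or ASQ-SE.
- **That T0 ADBB and EPDS are wrongly kept out of the ASQ-SE model.** Both overlap largely with the risk condition and depression status already among the family characteristics, so no such case is made here.
- **That every family will have a T0 value.** The measure is scheduled at T0, but the article itself plans multiple imputation unless more than 95% of observations are complete.

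**Conclusion.** The point holds for attachment. As written, the rule keeps T0 CIB sensitivity out of the SSP security and disorganisation models, although the trial collects it and the article itself gives the reason to use it. The cost is precision: a standard error larger than it need be by an amount that the covariate would cut by about 0.5% to 8%, or about 3 to 48 dyads on 250.

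This rests on three assumptions: a partial correlation of 0.1 to 0.4, which no document supplies; independent dyads, since clustering is ignored; and a T0 recording made before allocation is revealed. The article implies the last of these, because the psychologist who carries out the baseline assessments at the home visit opens the envelope to enrol the family.

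To read the omission as a bias or a false-positive risk would go beyond the documents. It is a free improvement, not the correction of an error.

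**What to change.** Amend the sentence in Statistical methods, or override it explicitly in the statistical analysis plan before allocation is unblinded, along these lines:

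> Secondary endpoints without their own T0 value are adjusted for the family characteristics. The continuous SSP security and disorganisation scores are adjusted in addition for T0 CIB maternal sensitivity.

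The T0 Bayley cognitive score may be added for Bayley language, stated openly as an assumption that it is prognostic. ASQ-SE can stay as it is. The change should be confined to the continuous attachment scores: in a logistic model for attachment categories, an added covariate also changes the conditional odds ratio being estimated.

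The cost is one sentence and about one degree of freedom per model. No new data are needed, and missing T0 values fall under the multiple imputation already planned.

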## Discussion

The protocol describes an experimental evaluation of an indicated brief manual- and group-based parenting educational program to enhance parental sensitivity and attachment compared to care as usual in a large community sample. This is an evaluation that has not yet been made in Denmark or internationally. Results will provide new evidence regarding the efficacy of a short term indicated parenting group program developed in the Unites States when implemented in a Scandinavian country. Further, COS-P is a promising approach as health nurses can be trained COS-P therapists in a future up-scaling. The efficacy of COS-P will be compared to the efficacy of Care as Usual (CAU) offered in Copenhagen to families identified to be at risk and in need of support. Results from this study will inform the City of Copenhagen of whether offering a systematic manual based short term parent intervention is more efficient in targeting infant mental health risks than what is currently offered as indicated prevention. Further, as we are collaborating with economist the study will provide knowledge of the cost-effectiveness of COS-P compared to CAU in the City of Copenhagen. If proved effective the study will represent a notable advance to initiating the COS-P intervention as part of a better infant mental health strategy in Denmark. Conversely, if this system is similar or inferior to the current system, this is also important knowledge in regard to preventing infant mental health risks in a cost effective way in a general population.

### Harms

The program consists of ten group 90 min COS-P sessions at UCPH Babylab. All participants are parents being challenged by maternal depression and/or infant social withdrawal in the first year of their baby’s life. During the period of COS-P intervention the mothers are assessed with EPDS to monitor her level of depression. Likewise, the infants showing signs of infant withdrawal are assessed with the ADBB to monitor the level of social withdrawal during the intervention period. At least for some individuals, the participation in a group may be experienced as a challenge, as well as the level of time consume to participate in COS-P may be a challenge for some. Most sessions are held late afternoon to promote the participation of the partners, as well as child minding facilities are offered during the COS-P sessions to ease the practical challenges of the families’ participation in COS-P. Further, as previously explained, participation is entirely voluntary and a decline to participate does not in any way affect assess to family services provided by the municipality. For these reasons, we expect the intervention to be associated with very low risk for participants.

### Registration

The project is registered with ClinicalTrials.gov: ID: NCT02497677. Registered July 15 2015

## Abbreviation

CIMHP: Copenhagen infant mental health project
